#### Nominated consultee opinion

In the situation where the patient has died, a nominated consultee will be appointed. The nominated consultee may include an independent mental capacity advocate appointed by the NHS Hospital Trust or an independent doctor (i.e. not involved in the trial). The opinion of the nominated consultee will be sought in the same manner as for the personal consultee. A nominated consultee will also be approached in the rare situations where no personal consultee is available (or one is available, but does not wish to be consulted). Upon the patient’s recovery, the patient will be approached directly for informed deferred consent. The patient’s decision will be final and will supersede the nominated consultee, where there is disagreement.

#### Discharge prior to consent being confirmed

In the situation where the patient is discharged from hospital with mental capacity prior to confirming their consent decision, an experienced member of the site research team with knowledge of intensive care will attempt a phone call to the patient as soon as reasonably practical, such as within 2–3 working days following ultimate hospital discharge to inform them of their involvement in our study; provide information about the trial; and seek their consent. The telephone consultation should be witnessed by another member of staff. The patient information sheet may be sent to the patient by email or by post. The outcome of the telephone call will be documented and signed by the person seeking consent on the telephone consent form, countersigned by the witness. Prior to contacting the patient, the member of the local research team should check the participant’s electronic record to ensure there is no evidence that this is not appropriate, for example that their general practitioner or hospital has not issued a notification of death.

If there is no response to at least three telephone call attempts, or where no telephone number for the patient is documented, then the patient will be notified of their participation by post. The patient will be sent a patient notification letter, personalised by the most appropriate clinical/research team member, and a copy of the PIS, again following review of the patient’s electronic record for updates on their clinical condition. The letter will direct the patient to the PIS for detailed information on the trial and provide contact details for if the patient wishes to discuss the trial further or to opt out. In addition, the letter will confirm that the participant’s data will be included in the trial unless they notify the site research team otherwise.

Both methods described above will provide patients with the opportunity to opt out of ongoing data collection or follow-up questionnaires. A decision to opt out during the telephone call will be documented by the person seeking consent on the telephone consent form. For the postal approach, the patient can actively opt out by using the telephone contact details provided on the PIS, at any point during the trial.

If the participant is transferred to another hospital participating in the trial before the consent procedures are complete, then the local research team will contact the research team at the receiving hospital to hand over the consenting procedures.

#### Refusal or withdrawal of consent

If a patient declines informed deferred consent, or a consultee advises that they believe the patient would not choose to participate in the trial, and if a patient or their consultee (personal or nominated) withdraws consent/opinion at any time during the trial—this decision will be respected and will be abided by. All data up to the point of this decision will be retained in the trial, unless the patient or consultee requests otherwise.

For patients who decline informed deferred consent, or a consultee advises that they believe the patient would not choose to participate in the trial, but do not request removal of all data, the site will enter minimal pseudonymised data required for the primary outcome only. The justification for this is that as deceased patients cannot refuse consent to continue in the trial, excluding primary outcome data from the cohort of patients who survive to decline informed deferred consent would introduce substantial bias and impact upon the safety monitoring/reporting and, ultimately, the scientific validity of the trial and may prevent evidence of significant clinical benefit from being detected. No patient identifiable data will be recorded, and no further contact with the patient/consultee about the trial will be required.

### Study stopping rules

The study may be prematurely discontinued by the chief investigator (CI) or funder based on new safety information or for other reasons that come to light, including a lack of recruitment, that indicate the study should be discontinued.

### Safety

Adverse event (AE) reporting will follow Health Research Authority guidance on safety reporting/Medical Devices (MEDDEV) guidance (https://ec.europa.eu/docsroom/documents/16477/attachments/1/translations).

Severity and causality of each with use of the device as per the above guidance. Adverse events and device deficiencies will be recorded by the research or clinical team and reported directly to the site principal investigator using the adverse event reporting form available here as a supplementary document at the above link and available here: https://ec.europa.eu/docsroom/documents/16477/attachments/2/translations. AEs identified in Tables 3 and 5 will be recorded daily by the research team whilst the participant remains within the trial.

An event assessed as ‘severe’ or ‘life-threatening’ will be considered a serious adverse event (SAE) in this trial. Considering that all eligible patients are critically ill and at increased risk of experiencing multiple AEs due to the complexity and severity of their condition, unexpected adverse events are only recorded if they meet the criteria for an SAE and are considered to have occurred as a consequence of the trial itself (i.e. deemed to be ‘possibly’, ‘probably’, or ‘definitely’ related to the trial procedures). Any SAEs, or device deficiencies that would have led to an SAE had suitable action not been taken, intervention not been made, or circumstances been less fortunate, will be reported by the sponsor of the clinical investigation to the UK National Competent Authority, using the standard MEDDEV SAE reporting form and summary tabulation immediately, or at most within the timelines laid out in the above guidance.

Staff members involved in the care of patients enrolled in the study will have the ability to report any concerns regarding adverse device effects and device deficiencies locally to the CI or directly to the central trial group via email contacts displayed at each trial centre.

Any concerns raised by trial teams at each centre, or the Trial Management Group, may result in a pause in the trial data collection pending formal review. This could include the formation of a formal Data Monitoring Ethics Committee.

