### Data collection by research team

A representative from the research team will review participants in the trial whilst the participant is in ICU throughout the period they are being proned, or the first working day afterwards if this has occurred over the weekend; once they have regained capacity; and at 3 months post discharge. They will collect patient data as detailed in Tables 4, 5 and 6 including standardised risk scoring measures used in ICU with potential relevance to our study (Waterlow, SOFA scores) [8, 9]. Data on device metrics will be obtained through discussion with clinical staff caring for the proned patient. They will ensure complete data sets are recorded through access to the clinical data entry form and spreadsheet, collect personal and nominated consultee opinions as required, and obtain patient consent. Patient notes will not be accessed by members of staff outside of those in the direct team until consent has been obtained.

**Table 4 Tab4:** Data to be collected by local research team—demographics

Patient metrics: Age, height, weight Frailty score Sequential Organ Failure Assessment (SOFA) [9] score on day 1 of proning Waterlow Pressure Ulcer Risk Assessment Scale on day 1 of proning [8] Pre-existing complications before day 1 of proning—see Table 6 ICU pressure sore risk score Medical comorbidities Diagnosis Device metrics—see Table 5 Proning complications—see Table 6

**Table 5 Tab5:** Data to be collected by local research team—device metrics (where clinical team who have used device are available)

Ease of introduction under the patient Ease of inflation/deflation Suitability of speed of inflation/deflation Ease of repositioning—head/arms Manual handling issue/concern Other comments

**Table 6 Tab6:** Data to be collected by local research team—proning complications

Pressure sore (face/chest/pelvis/knees/feet) Nerve injury (neck/arm/abdomen/leg) Blood vessel injury Skin abrasion Organ injury (liver/pancreas/genitals/ocular) Other	

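### The trial's SAE definition rests on severity grade alone, so a related event of moderate grade with lasting harm falls outside regulator reporting and, if unexpected and unlisted, outside recording

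*Protocol article*

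**What the plan says.** The Safety section opens by adopting outside guidance: "Adverse event (AE) reporting will follow Health Research Authority guidance on safety reporting/Medical Devices (MEDDEV) guidance". It refers severity and causality grading to that guidance. It then gives its own rule for seriousness: "An event assessed as ‘severe’ or ‘life-threatening’ will be considered a serious adverse event (SAE) in this trial". This is the only SAE definition in the article.

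The label is used in three places:

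- **Recording (Safety).** Because the patients are critically ill, "unexpected adverse events are only recorded if they meet the criteria for an SAE" and are also judged at least possibly related to the trial procedures.
- **Regulator reporting (Safety).** "Any SAEs, or device deficiencies that would have led to an SAE had suitable action not been taken", among similar near-miss conditions, "will be reported by the sponsor of the clinical investigation to the UK National Competent Authority".
- **Monitoring (Data monitoring plan).** SAEs, expressly as the protocol defines them, are one trigger for further monitoring of a site.

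Separately, the Safety section says: "AEs identified in Tables 3 and 5 will be recorded daily by the research team whilst the participant remains within the trial". Table 3 lists repositioning complications. Table 5 lists device-usability items. The proning complications are in Table 6 (Data collection by research team), which includes "Nerve injury (neck/arm/abdomen/leg") and "Organ injury (liver/pancreas/genitals/ocular").

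**The concern.** Severity and seriousness are different attributes. Severity grades how intense an event is; seriousness concerns what it leads to. A nerve injury can be moderate in intensity and still leave a permanent deficit. A definition built only from intensity words does not reach that case.

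This matters because safety is part of the stated aim, the Sample size section indicates that the device had not been trialled on patients when the study was planned, and the Statistical analysis section expects the findings to support planning for regulatory approval. A related injury with lasting effect is the kind of event that the regulator and a later, larger trial would want to see classified correctly.

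**Working it through.** No arithmetic applies. The check was to follow the definition through each place that uses it, and to look for any other seriousness criterion in the article. None was found: death, lasting impairment and prolonged stay are not named as SAE criteria anywhere.

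Applying the rules as written to the relevant kinds of event gives:

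| Event, related to device or procedure | Collected or recorded? | SAE under the stated rule? | Reaches the regulator by the SAE route? |
|---|---|---|---|
| Graded severe or life-threatening | Yes | Yes | Yes |
| Moderate grade, lasting harm, listed in Table 3 or 6 | Yes, as a complication | No | No |
| Moderate grade, lasting harm, unexpected and unlisted | No, it fails the recording condition | No | No |

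Three further points follow from the text.

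1. The device-deficiency limb of regulator reporting inherits the same definition, because it asks whether the deficiency would have led to an SAE. A deficiency that could have caused a moderate but lasting injury is outside it too.
2. The recording condition has two parts, SAE status and relatedness. Relatedness is a reasonable filter in this population. The gap comes from the SAE part.
3. The sentence on daily recording points to Table 5, which holds items such as ease of inflation. Table 6, where the injuries with possible lasting effect are listed, is not named there. Table 6 is still collected under Data collection by research team, so this is a cross-reference to reconcile and not a loss of those data.

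**The case against.** The strongest reply is that the section adopts HRA/MEDDEV guidance for reporting, including forms and timelines, and that this guidance may carry its own definition of seriousness. The SAE sentence is also worded as a sufficient condition and does not say that nothing else counts. The guidance is not among the documents, so its content cannot be checked here. The reply narrows the point but does not remove it. The SAE sentence applies expressly to this trial, it is the only criterion given, and the Data monitoring plan relies on the protocol's definition. Site staff would have two possible sources for one definition.

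A reader might also infer more than the text supports:

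- **That deaths would be missed.** Death is not named, but a fatal event would almost certainly be graded severe or life-threatening. The practical gap is lasting harm at moderate grade.
- **That Table 6 injuries drop out of the dataset.** They do not. Table 3 complications are entered after each repositioning and Table 6 complications are collected by the research team, neither with a severity threshold. The recording condition applies to unexpected events only. Both tables also have an open category for other complications, which might catch some unlisted events, although the article does not say that an event failing the Safety rule should be entered there.
- **That pausing or stopping depends on the SAE label.** It does not. Study stopping rules refers to new safety information or other reasons, and Safety allows a pause on any concern raised by site teams or the Trial Management Group. Staff can also report device concerns directly to the central group.
- **That the two repositioning methods are treated differently.** The definition makes no such distinction.

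Finally, an unrestricted criterion of prolonged stay would capture much background illness in ventilated, proned patients, which is the problem that the recording restriction is meant to avoid. That objection stands and shapes the fix.

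**Conclusion.** The point holds in a limited form. Under the rule as written, a related event of moderate grade with lasting consequence is not an SAE. If listed, it is collected but not sent to the regulator by the SAE route, and it does not meet the SAE trigger for extra monitoring. If unexpected and unlisted, the Safety rule does not have it recorded.

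The number of such events cannot be derived from the article, which gives no rates for them. The direction is under-classification. The staff-time analysis is untouched, and the secondary outcomes are descriptive. The conclusion assumes that sites apply the trial-specific sentence as their working definition. If they apply an outcome-based definition from the adopted guidance instead, the gap may close in practice, but the two texts would still need to be reconciled. The change is worth making because it is cheap and concerns safety reporting for a device not previously trialled on patients.

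**What to change.** Separate seriousness from severity in the Safety section, in one of two ways:

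- state that the adopted guidance's definition of seriousness governs, and remove the severity-only sentence; or
- define seriousness by outcome: death, a life-threatening event, lasting impairment, or intervention needed to prevent one of these, with prolonged stay counted only where it is judged related to trial procedures. Keep severity as a separate grade.

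Use that one definition for recording unexpected events, for regulator reporting (including device deficiencies) and for the trigger in the Data monitoring plan. Reconcile the cross-reference to Tables 3 and 5 in the daily-recording sentence with Table 6.

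The cost is a protocol wording change, with the approvals and site notification that any amendment needs, and probably a few more SAE forms in 30 patients. Sample size, randomisation and the primary analysis do not change. Recruitment began in May 2025, so events already collected under Tables 3 and 6 should be reclassified under the new definition. Unlisted events that were not recorded can be recovered only as far as site records allow.

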### Statistical analysis

We will test for a treatment effect using a linear mixed effects model with repositioning time as the response, fixed effects for site, sequence group assignment, and repositioning method, with random effects for individual to account for repeated measures. Analysis of the number of staff needed to carry out the repositioning procedures will take a similar approach, using a mixed effects cumulative logistic model to account for the discrete nature of the data. All tests will use the conventional 5% significance level.

No imputation or other statistical adjustments for missing data will be undertaken for these analyses. All recorded measurements of repositioning time and the number of staff needed within each proning session for the analysis, which means there is a very low chance that patients will be excluded from the analysis based on missing data. It will not be possible to tell if data on a repositioning exercise is fully missing. Whilst estimates of the treatment effect stratified by case complexity and BMI would be of interest, no sub-group analyses are planned as these would not be statistically reliable given the size of the trial.

This trial is focused on establishing efficacy in relation to the core repositioning outcome. Demonstrating efficacy is a necessary step before progressing to a larger trial that could robustly assess clinical outcomes, such as the prevention of pressure ulcers, which are relatively rare and require significantly larger sample sizes to detect with confidence. As such, this study is not powered to detect statistically significant effects in secondary outcomes, and formal hypothesis testing for these could be misleading. However, collecting and reporting detailed summary statistics will allow assessment of trends, variability, and effect sizes, which are essential for designing an appropriately powered future trial.

Summary statistics and distributional properties for the secondary outcomes will be produced and reported to inform any future studies focusing on patient outcomes and provider attitudes. The distributional properties of the continuous variables will be examined with histograms and boxplots. Participant characteristics and outcomes will be summarised using descriptive measures: mean (standard deviation) or median (interquartile range) for symmetric or skewed continuous variables, respectively; number (percent) for categorical variables. The findings from this study will provide essential data on usability, safety, and performance under clinical conditions, supporting the next stages of product development. These include refinement of the design, the definition of performance claims, and planning for regulatory approval.

The health economic evidence will be compiled to allow cost-effectiveness analysis of the BathMat technology relative to alternative technologies. Health economic measures will be reported in cost per QALY with mean and standard deviations, as with other secondary outcomes, to contribute towards the health economic argument for use of the device. In addition to standard health economic measures, bespoke information specific to the trial context will be collected. This tailored methodology will capture effects which cannot be captured by standard health economic measures. For example, the relationship between the number and frequency of repositioning (and associated costs), as well as the potential impact on complications, follow-up treatment, and subsequent litigation, cannot be fully captured using conventional methods alone.

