**Methods:**

The BathMat trial is a randomised, multicentre, single-blind crossover study of repositioning in ventilated proned patients in ICU using the BathMat vs conventional care. Ventilated patients who require proning will be randomised to be repositioned with standard care or the BathMat. The same repositioning method will be used throughout each proning session, but will alternate on subsequent proning sessions between BathMat and standard care. The primary outcome is the difference in total staff time (number of staff × total time taken) required to reposition a patient with the BathMat compared with standard care. Secondary outcomes are the number of repositioning exercises performed, the number of adverse incidents associated with repositioning, the ease of manual handling, and the health economic costs of the complications of proning.

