### Objectives and outcomes

See Table 1.

**Table 1 Tab1:** Objectives and outcome measures

Objective	Outcome measure	Source
Primary objective To investigate the staff time required to perform a proned patient reposition exercise. This will include the total number of staff required as well as the duration of the exercise	a. Difference in number of staff required to reposition each patient b. Difference in time required to reposition each patient	The number of staff required to reposition the patient and the time required will be collected by clinical teams by scanning a quick response (QR) code unique to each patient every time a patient is repositioned
Secondary objectives a. Assessment of the number of repositioning exercises undertaken for each patient within a proning intervention b. The number of minor or major adverse incidents associated with repositioning patients whilst in the prone position. This includes events such as line or tube displacement c. The manual handling requirement to reposition d. In patients who suffered a major or minor adverse event (as defined in secondary outcome b), assessment of the healthcare costs relating to that event at 3 months following ICU discharge	a. Number of documented repositioning exercises b. Adverse events documented c. Difference in Likert scale measure of difficulty of repositioning between control and intervention groups d. Healthcare costs of adverse event at 3 months post discharge	a. Clinician form entry from QR code (as above) b. Clinician form entry from QR code (as above), research team form entry c. Clinician form entry (from QR code as above) d. Research team form entry

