#### Sample size

A sample size of 30 patients was determined from statistical analysis of the proposed trial. This is sufficient to detect a decrease in repositioning time of at least 10 min with a power of over 95%. An estimated 10-min improvement was identified via a preliminary unpublished volunteer study. This was determined to be the optimal route to estimate the approximate magnitude of time saving before the device was trialled on patients as part of the proposed clinical study.

Power calculations were carried out using Monte Carlo sampling to allow for variability in the number of repositionings per proned session and the number of proned sessions per patient. In addition to standard deviation assumptions, 2–4 repositionings per proning session were used (randomly sampled with proportions (1/5, 3/10, 1/2)) and a dropout rate of 1/3 after the first session. The repeated measurements for each patient were simulated using a correlation of 0.7 within the same treatment and 0.3 between the two treatments.

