### Data entry by clinical team

When enrolled patients require repositioning, the total staff time taken to reposition must be recorded—this is the primary outcome measure. An online clinical data entry Microsoft form, accessible via QR code or hyperlink at the patient’s bedside using any device, will allow staff to submit data from Table 2. Table 3 details domains for repositioning complication. The live Microsoft form will collect patient data linked to the participant’s study number and be managed by the central study team. It will not contain any other identifiable information.

This requires the bedside nurse primarily responsible for patient care to record the time (HH:MM 24-h clock format) at each point of repositioning as stated below, and the number of staff required to do so, by scanning the ‘repositioning QR code for bedside nurse’ unique to that patient or using the appropriate unique uniform resource locator (URL). Time should be rounded to the nearest minute, without the use of decimal places or seconds. The form must be completed after each repositioning manoeuvre and does not require any timing calculations by clinical staff. Instead, the form asks for four data points from the bedside nurse regarding the primary outcome:Repositioning start time: The time when the first staff member required to reposition the patient (in addition to the bedside nurse) enters the bed space to begin repositioning.Repositioning ready time: The time when the last member of staff required to reposition the patient has arrived in the patient’s room or bedspace.Repositioning stop time: The time when the last member of staff who was drawn in to assist the bedside nurse with repositioning has left the patients room or bedspace.The number of staff taken to reposition: Includes all staff (including the bedside nurse) who have helped in the repositioning manoeuvre. This does not include anyone outside of the patient’s room or bedspace who was available for help, and not actively involved in the repositioning manoeuvre.

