It should be noted that statistical analysis will be performed on differences in the time required to gather staff (the difference between repositioning start time and repositioning ready time) and the time required to perform the repositioning exercise (the difference between the repositioning ready time and the repositioning stop time). However, the overall repositioning time (the difference between repositioning start time and repositioning stop time) will be used in the calculation of the primary endpoint.

One member of clinical staff will be expected to complete this data entry exercise every time a patient is repositioned (with or without the BathMat). This is expected to be the bedside nurse looking after the patient, but may be contemporaneously delegated by them to any suitably trained individual.

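### The declared primary endpoint, staff number × time, is defined inconsistently and has no model-based test or power; the models and sample size address its components

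*Protocol article*

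**What the plan says.** The protocol article describes the primary outcome in two ways.

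- **As a product.** Abstract, Methods: "The primary outcome is the difference in total staff time (number of staff × total time taken) required to reposition a patient". The Aim is likewise framed as a change in total staff time. Under Data entry by clinical team: "the total staff time taken to reposition must be recorded—this is the primary outcome measure". That section also makes the start-to-stop time an input to the primary endpoint, not the endpoint itself.
- **As two separate measures.** Table 1, primary objective: "a. Difference in number of staff required to reposition each patient b. Difference in time required to reposition each patient". The product does not appear there.

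The analysis and the power calculation are then fixed as follows.

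- **Statistical analysis:** "We will test for a treatment effect using a linear mixed effects model with repositioning time as the response". Staff number gets its own cumulative logistic mixed model. "All tests will use the conventional 5% significance level". Secondary outcomes are to be summarised, not formally tested.
- **Sample size**, on 30 patients: "This is sufficient to detect a decrease in repositioning time of at least 10 min with a power of over 95" per cent.
- **Data entry by clinical team** adds that "statistical analysis will be performed on differences in the time required to gather staff", and also on the time to carry out the manoeuvre.

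**The concern.** Endpoint, model and power should refer to the same quantity. Here the declared quantity is staff-minutes, the model responses are minutes and a staff count, and the power is for minutes. The device is expected to save staff as well as time, so a test of elapsed time captures only part of the intended effect.

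At stake is whether the trial can report the result named in its title and aim with an estimate, an interval and a test. The article says the findings will support performance claims and regulatory planning. If the choice among staff-minutes, time and staff number is left open until the data are in, it could look data-driven.

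**Working it through.** **1. Does repositioning time mean staff time?** No. Data entry by clinical team defines overall repositioning time as start to stop. Statistical analysis models staff number separately, and Sample size states the effect in minutes. The response of the main model is therefore elapsed time.

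**2. Can the two planned models be combined into staff-minutes?** Write S for staff number and T for elapsed time. The mean of the product is

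E(S × T) = E(S) × E(T) + Cov(S, T).

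The time model gives a mean difference in T. The staff model gives a cumulative odds ratio, which is not a difference in mean S. Fitted separately, neither gives Cov(S, T). No effect in staff-minutes follows from the two results.

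**3. The stated power figure.** Inputs from Sample size:
- N = 30 and a difference of 10 min
- 2, 3 or 4 repositionings per session with probabilities 0.2, 0.3 and 0.5
- one third dropping out after the first session
- correlation 0.7 within and 0.3 between treatments

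Allocation is 1:1. The SD was used but is not given, so it was varied. Four sites, a two-sided 5% test and a known correlation structure were assumed.

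The standard error came from generalised least squares with site, sequence and method as fixed effects, averaged over 400 simulated designs. Power = Φ(10/SE − 1.96).

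| SD (min) | At most 2 sessions (SE ≈ 0.214 × SD) | Up to 5 sessions (SE ≈ 0.208 × SD) |
|---|---|---|
| 10 | 99.6% | 99.7% |
| 12 | 97.1% | 97.8% |
| 13 | 94.7% | 95.8% |
| 15 | 87.5% | 89.3% |
| 20 | 64.9% | 67.5% |

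Power above 95% is attainable if the SD is about 13 min or less. It cannot be confirmed without the SD, and it concerns elapsed time only.

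**4. What 10 min means in staff-minutes.** The Background gives 5 staff falling to 2, and 30–60 min for a standard repositioning. For the same 10-min saving:

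- staff stay at 5: 5 × 10 = 50 staff-min
- staff 5 to 2, control time 30 min: 5 × 30 − 2 × 20 = 150 − 40 = 110 staff-min
- staff 5 to 2, control time 60 min: 5 × 60 − 2 × 50 = 300 − 100 = 200 staff-min

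With the Background's full claim of a fall to 10 min, the difference is 150 − 20 = 130 to 300 − 20 = 280 staff-min. A 10-min target therefore does not fix a target in staff-minutes. The article gives no SD or correlation in that unit, so its power cannot be derived.

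**5. The staff cut alone.** At unchanged duration T, staff time goes from 5T to 2T, a fall of 1 − 2/5 = 60%. The difference in elapsed time is zero, so the powered test does not register it. The staff model would.

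**6. Two tests at 5%.** If success on either one sufficed, familywise error under independence would be 1 − 0.95² = 0.0975. Positive correlation would lower it. If both were required, there would be no inflation. The text says neither.

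**The case against.** The strongest reply is that Table 1 is the formal outcomes table. Under its definition each primary measure has a model and a test, so the trial is not left untested. That stands. It shows that the definition is inconsistent, and it does not supply a test of the product that the abstract declares.

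A second reply is that the analysis plan, which is not shown, may settle the matter. This would answer an omission. Here the article itself names the model responses and the unit of the power calculation, and both differ from its declared endpoint.

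A reader might also infer more than the documents support:

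- **That staff time will go unreported.** The article says outcomes will be summarised descriptively, and a summary of staff time by method fits that text. What is missing is a model-based estimate and test.
- **That four outcomes are each tested at 5%.** Only time and staff number have explicit tests. Gathering and performing time are promised statistical analysis, which need not mean a decisive test. They also add up exactly to overall time, so an error rate for four independent tests would not apply.
- **That any one significant result counts as success.** The article does not say so. The 9.75% is conditional on that rule.
- **That time might rise while staff time falls.** This is arithmetically possible, but the protocol's own figures have both falling.
- **That the power figure is wrong.** It is already labelled as repositioning time and is attainable at a plausible SD.

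**Conclusion.** The point holds as an inconsistency within the protocol. The primary outcome is a product in the abstract and two separate measures in Table 1; the models follow Table 1, and the power covers elapsed time only. As written, the declared endpoint has no model-based test, effect estimate or power.

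The practical size is the part of the effect that the powered test misses: a 60% fall in staff time if staff drop from 5 to 2 at unchanged duration, visible only in the separate staff model. This rests on the Background's staffing figures.

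The open decision rule is a lesser matter. It is worth about 9.75% familywise error at most under independence, and only if either test alone could declare success.

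**What to change.** - **Endpoint.** In Table 1 and Statistical analysis, name staff-minutes per repositioning exercise (staff number × start-to-stop time) as the single primary endpoint.
- **Analysis.** Make it the response of the mixed model, log-transformed for example if skewed, as the one confirmatory test at 5%. Report overall, gathering and performing time and staff number as supportive estimates with 95% confidence intervals. This also removes the question of which test decides.
- **Sample size.** State that the figure of over 95% does not apply to the primary endpoint. Then either add a simulation in staff-minutes with its assumed difference and SD stated, or say that power for staff-minutes was not calculated.

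No new data are needed, because times and staff number are already recorded at each exercise. The cost is some wording, new assumptions for any simulation (rerunning the existing one is not enough) and possibly a less favourable power figure. Recruitment is expected to finish around July 2026; the change should be made and dated before outcome data are compared by method.

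Keeping time and staff number as co-primary or ordered endpoints with a stated rule would also be coherent. The abstract and aim would then have to change, and the trial would still give no effect in staff-minutes.
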